#### Qualitative data

Ethnographic approaches have had some success in describing the health risks of vulnerable, global populations. We have previously developed a locally validated seven-category framework for qualitatively describing the implementation processes [48]. Data collection will be implemented in three phases. The first phase is largely exploratory, in which we develop an exhaustive list of potential categories related to the existing seven-domain framework. The aim is to validate the existing framework and to elaborate other factors that might lie outside the framework or that challenge how the framework resonates with experiences on the ground. The second phase will consist of participant observation, FGDs and free listing exercises with clinicians, health care facility management team members, and patients. In addition to KIIs and FGDs, ideals expressed in interviews and group discussions will be observed and compared to actual practice. The third phase consists of managing, organizing, and analyzing the qualitative data collected in phases one and two to develop a comprehensive list of strengths, weaknesses, and opportunities. The conclusions of these different methods will be used to help plan for future implementations of similar interventions.

All qualitative data will be stored on a Research Electronic Data Capture (REDCap) database. REDCap is a secure, web-based application designed to support data capture for research studies, providing (1) an intuitive interface for validated data entry, (2) audit trails for tracking data manipulation and export procedures, (3) automated export procedures for seamless data downloads to common statistical packages, and (4) procedures for importing data from external sources. REDCap user access will be defined so that researchers only have access to de-identified study data.

Qualitative data will be reviewed after they are aggregated on a weekly basis following data collection events. Once data are stored into REDCap, all paper copies of data form will be stored in a locked cabinet within a locked room in Bayalpata Hospital or Charikot Hospital. Once all data are fully inputted and validated for quality, all paper copies will be destroyed. REDCap data will be deleted 1 year after study end.

### Data analysis

#### Analysis for specific Aim 1: effectiveness

For assessing effectiveness, we focus on three population health outcomes as shown in Table 1. We hypothesize the integrated intervention will lead to a 15% increase in the institutional birth rate—Primary Outcome 1—among reproductive age women in the study population over the three-year study period. We hypothesize the integrated intervention will lead to a two death per 1000 reduction in the under-two mortality rate—Secondary Outcome 1—in the study population over the three-year study period. We hypothesize the integrated intervention will lead to a 10% increase in modern PPCPR—Secondary Outcome 2—among recently delivered women (defined as having had a live birth in the preceding 24 months) in the study population over the three-year study period.

**Table 1 Tab1:** Evaluation framework

Aim	Outcome/RE-AIM element	Indicator	Definition
Effectiveness	Primary outcome 1: institutional birth	Institutional birth rate	% women delivering at a facility with a skilled birth attendant
	Secondary outcome 1: child mortality	Under-2 mortality rate	# child deaths before age 2 per 1000 live births
	Secondary outcome 2: post-partum contraception	Post-partum contraceptive prevalence rate	% post-partum women using a modern form of contraception
Implementation	Reach	Home visit coverage	-% children under age 2 years receiving a CHW home visit, measured monthly -% pregnant women receiving a home visit by a CHW, measured monthly -% reproductive aged women receiving a pregnancy surveillance home visit, measured quarterly -% postpartum women receiving 1+ balanced counseling session, measured biannually
		Group participation	% scheduled participants completing group sessions, measured monthly
		Session completion	% scheduled group sessions completed, measured monthly
		Demographic, geographic barriers and facilitators	Mapping households, describing barriers/facilitators to individuals’ access, and identifying contributors to variation/inequities
	Efficacy	Pregnancy identification	% all pregnancies identified in first 12 weeks
		ANC completion	-% women at 9+ months gestation completing 4+ ANC visits at a health care facility and eligible for government financial incentive out of total # of women delivered, measured monthly -% pregnant women who receive an obstetric ultrasound by their due date, measured monthly -% pregnant women with prenatal labs completed by 6 months gestation, measured monthly
		Exclusive breastfeeding prevalence	% infants age 0–5 months who are exclusively breastfed, measured monthly
		Pediatric pneumonia incidence	# new cases of pneumonia in children under age 2 years, measured monthly
		Pediatric stunting prevalence	# children under age 2 years whose length-for-height/height-for-age is < 2 SDs WHO child growth standards median, measured monthly
		Unmet contraceptive need	% eligible reproductive-age women within 12 months postpartum who desire to either stop or postpone childbearing for the next 2 years who are not currently using a modern contraceptive method or have a repeat unintended pregnancy while not using modern contraception, measured monthly
		Contraception method mix	% women within 12 months postpartum using each method of modern contraception, measured quarterly
		Contraception initiation and continuation	Contraceptive initiation and continuation probabilities at 3, 6, 12, and 24 months after method initiation, measured quarterly
	Adoption	Village cluster adoption	% intended village clusters receiving intervention
		Timely adoption	% intended village clusters rolling-out intervention within 3 months of schedule
		CHW adoption	-# CHWs hired/trained in intervention implementation -# CHWs who resign
		Government adoption	-% group care sessions co-facilitated by a government health worker -# collaborative care meetings with government partners during implementation
	Implementation	Supervision model	-% scheduled supervision field visits completed, stratified by CHN and district -# data review meetings held with CHWs and CHNs, measured quarterly
		Group care content fidelity	% planned topics covered at each session, measured monthly
		Home visit fidelity	-% women with “adequate” number of home visits received -% appropriate ANC topics covered during each pregnancy care home visit -% child health topics covered during each under 2 home visit -% balanced counseling points covered at each postpartum contraception counseling session, measured biannually
		Referral completeness	% referrals completed as prescribed by the clinical algorithm
		Implementation challenges	Exploratory and hypothesis-generating as revealed through FGDs and KIIs
	Maintenance	Total intervention cost	Cost of each intervention component and total costs using the Time Defined Activity Based Costing (TDABC) method
		Cost per unit	-Intervention cost per 1000 people -Projected cost to scale intervention nationally
		Maintenance cost	% breakdown of maintenance costs (personnel, materials, and other)
		Facility vs. community costs	% of costs of health care divided between facility level and community level
		Geographic cost variation	Variation of costs between village clusters and districts
		Out-of-pocket patient costs	% costs of health care divided between facility level and community level
		Integrated intervention cost-effectiveness	Pre/post intervention marginal effectiveness for primary outcomes, not account for secondary effects (e.g., increasing the costs of care through increased cesarean sections)

The primary predictor is the effect of the intervention measured in 3-month intervals throughout the study period, comparing to the FCHV standard-of-care control at baseline. Calendar month will be included as a separate covariate to control for the overall secular trend. Variables will be considered as both nominal and continuous (linear effect) predictors, and the generalized linear model framework will be used to estimate effect of time-varying repeated measure intervention implementation over the several steps of the wedged design. Differential impact from time of intervention will be evaluated with test of month × intervention interaction. Models will be fit using generalized estimating equations, e.g., using SAS Proc Genmod, to calculate valid standard errors in the presence of repeated measures over time and possibly correlated outcomes at the village cluster level. Assumptions of over- or under-dispersion will be examined closely, and an estimated scale parameter or negative binomial models will be used as needed.

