Recognizing that women were being missed and identified late in their pregnancies, *Possible* started pregnancy surveillance for all reproductive age women. Every 3 months, women are asked about their last menstrual period and offered a pregnancy test if pregnancy is suspected. Early pregnancy detection is linked to better birth outcomes, likely due to early initiation of ANC and reduction of high risk behaviors [31]. Additionally, early pregnancy awareness is important to help women with undesired pregnancies access safe and legal abortion care.

In an effort to build social support and women’s empowerment, *Possible* began group care, based upon Centering Pregnancy [32, 33], to complement home visits. This is a model of facilitated groups throughout pregnancy that include health assessments and self-care activities; education, support, and socialization; and ongoing outcome evaluation. By bringing together pregnant women of similar gestational ages, the program makes efficient use of time for antenatal counseling and testing, while allowing facilitators to focus on women’s experiences and concerns. Women also develop a network of peer support during what can be a challenging time. In the rural Nepal context, these groups became an important modality for strengthening care and increasing trust in local village clinics and decentralizing ultrasound and prenatal lab services (Bangura A et al: Measuring fidelity, feasibility, costs: an implementation evaluation of a cluster-controlled trial of group antenatal care in rural Nepal, in preparation; Thapa P et al: Group compared to individual antenatal care: a cluster-controlled trial in rural Nepal, in preparation). These life-saving diagnostic services are not generally available at government clinics and enable CHWs to identify high-risk patients who may require referral to a higher level facility for further care and delivery.

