### Study population

The study population will include women of reproductive age (between ages 15–49) and children from 0 to 24 months of age enrolled in continuous surveillance, home-based care, and/or monthly group ANC led by *Possible’s* team in Achham and Dolakha. Specifically, this will include patients receiving health care services at Bayalpata Hospital in Achham and Charikot Hospital in Dolakha or household-level care through networks of CHWs across both districts.

Staff members involved in the program will be approached for key informant interviews (KIIs) and focus group discussions (FGDs). For all qualitative methods, we will use purposive sampling aiming to maximize heterogeneity across sex, socioeconomic position, health care issues, geographic location, age, caste-class, and other attributes. KIIs will be conducted with participants of the group ANC groups, recently delivered women, women receiving antepartum and postnatal home-based care, and reproductive age women receiving pregnancy screening. KIIs will also be conducted with team members who implemented the interventions, community leaders, and government leaders.

Participants eligible for inclusion in the study include the following: (1) married, reproductive-aged women 15–49; (2) reproductive-aged women 15–49; recently delivered in past 2 years; (3) reproductive-aged women 15–49 with active pregnancy during study period and identified by a CHW serving their village; (4) children aged 0–2 of recently delivered mothers (population 2 or 3 above); and (5) health care staff members including CHWs serving village clusters, research performance site employees involved in study design, program implementation, data collection, or data analysis processes. Study populations 1–4 must reside in either Achham or Dolakha.

Individuals meeting inclusion criteria, as stated above, will be included in the study without exclusion unless (1) individuals migrate from the study before completion of any of the integrated interventions or (2) individuals explicitly request exclusion from the study and decline to consent to the study.

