### Study design

This is a type 2 hybrid effectiveness-implementation research study examining an integrated RMNCH intervention. This intervention integrates the five evidence-based approaches described above, focused on the “golden 1000 days” from conception through age two. We plan to study the impact on population health outcomes using a pre-post quasi-experimental design with stepped implementation as it is rolled out by CHWs in Achham and Dolakha. We will assess the implementation process using the RE-AIM framework, closely examining reach, efficacy, adoption, implementation, and maintenance.

We will evaluate the intervention as it is rolled out in stepped implementation. Implementation will occur in sub-populations of about 20,000 at a time (including village clusters of 1000 to 6000 people). Full implementation of the integrated intervention in any sub-population will take 6 months. Approximately 80 clusters across the two sites will be involved in the study, with a total population of approximately 300,000. This is incorporated into the power calculations below.

In this pragmatic trial, village cluster units are determined by Nepal administrative boundaries. Enrollment and timing of enrollment are based upon local government decision-making and as such cannot be randomized. Data collection is developed and integrated within the routine course of care, because this is the approach we have found to be ethical, acceptable, and affordable in our context. This has the following implications: (1) the number of villages per cluster is variable, (2) interval between new clusters being ramped up can be variable from the scheduled start times, and (3) baseline data occurs at the beginning of each step rather than at study start.

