### Sample size

This implementation research study uses a census methodology rather than a representative sample. The programmatic intervention aims to reach all individuals within the catchment area population given the research performance site’s care mandate to serve this population. All individuals in the catchment area population, as defined under study site above, who meet the inclusion criteria will be approached for inclusion into the programmatic intervention, for which their de-identified clinical data will be analyzed towards the primary aim. The sample size is determined by the overall population covered in the two districts of 300,000, (rather than calculated via a sample size formula) within which we anticipate approximately 8000 deliveries per year or 12,000 during the first 18 months of the study during which enrollment will occur.

To calculate power for the primary outcome of institutional birth rate, we consider a Poisson regression model with 0.05 significance level and two-sided power of 80 or 90%. We further assume a 1-year exposure mean per child over the course of the intervention. We will consider models where the secular trend and other covariates explain 25 or 50% of the total variance in mortality. We assume intra-cluster correlation of outcomes would range from 0.2 to 0.8 for design considerations. Based on these parameters and recent advances in stepped wedge methodology [47], we calculated a design effect ranging from 0.3 to 0.8 to account for the wedge design. To be conservative, we further included a multiplicative design effect of 2.5 to account for cluster randomization, resulting in an overall design effect of 1.8 at a maximum.

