#### Analysis for specific Aim 2: RE-AIM implementation analysis

Here, we use the RE-AIM framework to evaluate the implementation process (see Table 1). (R)each in a remote area is vital to success. We will assess coverage of and participation in the integrated intervention for each reproductive age woman, pregnant and postpartum woman, and under-two child. Additionally, we will analyze barriers and facilitators to coverage and participation.

For (E)fficacy, we look at our integrated intervention’s ability to successfully identify pregnancies in the first trimester, pediatric cases of illness, and women with an unmet need for contraception. If these are successfully identified and appropriate care is delivered, then we will see an impact on the outcomes in Aim One. Additionally, we look at secondary outcomes not included as the main measures of effectiveness in Aim One: exclusive breastfeeding, modern contraception initiation and continuation, and government ANC visits.

Community level (A)doption is largely dependent upon the local political and governance context. Process measures for community-level adoption include the number of village clusters that roll out the intervention, the time to roll out relative to the stated target date, and the number of CHWs hired and trained. We will also assess commitment to the intervention and its various components through semi-structured KIIs with managers and CHWs.

We will assess (I)mplementation fidelity to the planned interventions. Using a qualitative approach, we will explore implementation challenges from a variety of perspectives, including key stakeholders, government partners, NGO staff, and community members. We will assess the quality of the intervention from the communities’ and patients’ perspective through in-depth KIIs.

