We will assess the all-inclusive costs of the interventions for (M)aintenance. The time-defined activity based costing method will be deployed for measuring costs at the beneficiary level by clearly identifying activities, personnel capacity required, materials, and equipment usage, as well as other general and administrative costs required. We will assess costs incurred for each intervention type, for varying levels of pregnancy care, and variability of costs across village clusters and districts. The cost measurement method will help in identifying cost optimizing methods without reducing effectiveness of the interventions to ensure judicious use of resources. The analysis will inform policy decisions that will lead to affordable and scalable interventions. This method will not fully capture all the economic benefits due to the intervention. Evidences suggest strong benefit-cost ratio for early investments in health with improved economic outcomes due to higher human capital, increased productivity and cognitive ability, and demographic dividends.

For each of the quantitative outcomes in RE-AIM, we will apply a similar generalized estimating equations methodology using 3-month intervals from data routinely collected by the mobile tool. For the qualitative component of the implementation analysis that includes FGDs, data analysis will be ongoing and iterative. Each step of exploratory interviewing and observation will shape the questions in the subsequent steps. The analysis of free list data will concentrate on two measures of an item’s salience. The first is the frequency with which any informant mentions each term, and the second is the salience index as computed by ANTHROPAC [49]. These measures will be used to estimate the salience of individual categories and to define the boundaries of the domain into which they fall. An additional measure of interest is the correlation between each informant’s responses and the group as a whole. Interviews and discussions will be partially transcribed and coded according to the Grounded Theory Method [50], a rigorous procedure for identifying themes in text and for developing theoretical models of the relationships among themes [51].

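### The first-trimester identification indicator counts pregnancies already past 12 weeks when surveillance starts, so it rises over each cluster's early intervals with no change in performance

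*Protocol article*

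**What the plan says.** Table 1 (under the Aim 1 analysis heading) lists pregnancy identification as the first Efficacy indicator, with the denominator spelled out: "all pregnancies identified in first 12 weeks". Unlike most of the Efficacy rows, it gives no measurement frequency.

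The Study population section admits women of reproductive age "with active pregnancy during study period and identified by a CHW serving their village". Neither that section nor Table 1 sets a limit on gestation at first contact.

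On how pregnancies are found, the section on evidence for the intervention says: "Every 3 months, women are asked about their last menstrual period and offered a pregnancy test if pregnancy is suspected".

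On timing, the Study design section says that "baseline data occurs at the beginning of each step rather than at study start".

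On analysis, the Aim 2 section says that for each quantitative RE-AIM outcome "we will apply a similar generalized estimating equations methodology using 3-month intervals from data routinely collected by the mobile tool". The Aim 1 model it follows estimates the intervention effect by 3-month interval against standard care at baseline, with calendar month as a covariate.

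On purpose, the Aim 2 section reads the Efficacy element as the intervention's "ability to successfully identify pregnancies in the first trimester".

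**The concern.** A pregnancy that is past 12 weeks before the first CHW visit scores as a failure however well the programme works. Such pregnancies are concentrated in the first sweep of each cluster. Later sweeps find mainly pregnancies conceived since the start, which can score either way. The percentage therefore rises with time since cluster start, the same axis on which the intervention effect is measured. Clusters start at different calendar times, so the calendar-month covariate does not remove a pattern tied to time since start.

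At stake is the reading of this indicator. The Aim 2 section treats early identification, together with finding child illness and unmet contraceptive need, as a step towards the Aim 1 outcomes. Turnover of the pregnant population could be reported as the programme becoming more effective.

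**Working it through.** The protocol gives no expected value for this indicator, so there is no figure to reproduce.

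**Inputs from the protocol**
- Surveillance round: every 3 months, taken as 13 weeks.
- Intended coverage: everyone ("The programmatic intervention aims to reach all individuals within the catchment area population").
- Achieved coverage: not given. It is itself a Reach outcome ("reproductive aged women receiving a pregnancy surveillance home visit, measured quarterly").
- About 8000 deliveries a year in 300,000 people; steps of about 20,000 people.

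**Assumptions not in the protocol**
- Gestation of 40 weeks and uniform conceptions.
- A pregnancy is detectable from *d* weeks after the last menstrual period, with *d* = 4 to 6.
- Constant performance throughout.

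**Stock at the start.** A step of 20,000 has 8000 × 20,000/300,000 = 533 deliveries a year. With *d* = 5, detectable ongoing pregnancies number about 533 × 35/52 = 359 (349 to 369 for *d* = 6 to 4). Of all women pregnant on the start date, 28/40 = 70% are beyond 12 weeks.

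**By date of identification, full coverage.** In the first sweep, gestation at the visit is uniform from *d* to 40, so the share at or below 12 weeks is (12 − *d*)/(40 − *d*). In later sweeps it is uniform from *d* to *d* + 13, so the share is (12 − *d*)/13.

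| *d* | First sweep | Later sweeps | Rise (points) |
|---|---|---|---|
| 4 | 8/36 = 22.2% | 8/13 = 61.5% | 39.3 |
| 5 | 7/35 = 20.0% | 7/13 = 53.8% | 33.8 |
| 6 | 6/34 = 17.6% | 6/13 = 46.2% | 28.5 |

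**By date of identification, coverage *c* per round.** The first-sweep share does not change. A pregnancy gets at most three rounds before 40 weeks, the third only if gestation at the first was below 14 weeks. Among identified pregnancies, the long-run share at or below 12 weeks is

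*c*(12 − *d*)/13 ÷ [*c* + *c*(1 − *c*) + *c*(1 − *c*)²(14 − *d*)/13].

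- *c* = 0.8: 50.0%, 43.9%, 37.7% for *d* = 4, 5, 6. Rises are 27.8, 23.9 and 20.0 points.
- *c* = 0.5: 36.4%, 32.2%, 27.9%. Rises are 14.1, 12.2 and 10.3 points.

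Simulation under the same assumptions agrees to within about a point. Early loss of 15% moves the rises by about 1 to 2 points. A first sweep spread over 6 months leaves the total rise the same but spreads it over two intervals.

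**By delivery date, full coverage, *d* = 5.** Women delivering in the first two intervals were 14 weeks or more at the start, so the share is 0%. In the third interval, gestation at the start is uniform on 1 to 14 weeks and the first visit uniform on 0 to 13 weeks later. The share seen between 5 and 12 weeks is (11² − 4²)/(2 × 13²) = 105/338 = 31%. After that it is 54%. Over *d* = 4 to 6 the rise from zero is 46 to 62 points.

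**By conception on or after the start.** With a first sweep of one quarter and *d* = 5, simulation gives 53.6% in the first interval and about 54% later, so no artificial rise. With a 6-month first sweep, a rise of about 4 to 12 points across the coverages tested remains, in the first interval only.

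**The case against.** **The article is condensed and gives no rule for assigning a pregnancy to an interval.** This is true, and such rules often sit in an analysis plan. Assigning by conception after the start would nearly remove the effect. But the denominator itself is stated, it is all pregnancies, and eligibility confirms that ongoing ones enter. Followed as written, the definition misleads.

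**Late pregnancies at the start represent the control condition.** These women passed their first trimester without CHW surveillance, so moving from them to later women might be called the intended pre-post contrast. This does not rescue the indicator. The Aim 2 section reads it as the intervention's own ability to find pregnancies early, and a baseline of almost no CHW identification, because CHWs were not yet there, says nothing about that ability.

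**The size is uncertain.** This stands. A reader might infer that the artefact is at least 30 points. The documents do not support that as a floor: coverage is an outcome rather than a fixed quantity, and at 50 to 80% coverage the rise by identification date is about 10 to 28 points.

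**Later improvement could still be seen.** This also stands. A reader might infer that the study could not tell whether surveillance improves. At constant performance the series levels off after the early intervals, and the plan allows nominal as well as linear predictors, so later change remains visible.

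**Quarterly visits cannot reach 100%.** A reader might add that the indicator is judged against an unattainable target. The protocol sets no target for it, so there is nothing to correct.

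**Conclusion.** The concern holds for the denominator. Counting all pregnancies builds an artificial rise into the early intervals of each cluster, aligned with time since start and not removed by calendar month. With 40-week gestation, uniform conceptions and detection from 4 to 6 weeks, the rise by date of identification is about 28 to 39 points at full quarterly coverage and about 10 to 28 points at 50 to 80% coverage. By delivery date it is up to about 60 points at full coverage. Restricted to conceptions after the start and indexed by conception, it is near zero.

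The distortion affects one implementation indicator. It does not touch institutional birth, under-two mortality or postpartum contraception. The Table 1 indicator on prenatal labs by 6 months is open to an effect in the same direction, but its later cut-off catches fewer ongoing pregnancies and its size has not been worked out.

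**What to change.** In Table 1, restrict the denominator of the pregnancy identification indicator to pregnancies whose last menstrual period falls on or after the cluster's start date, and assign them to 3-month intervals by that date. Report pregnancies already under way at the start, the first sweep, separately. Consider the same restriction for prenatal labs by 6 months.

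A looser alternative is to admit pregnancies at or below 12 weeks when surveillance starts. It keeps more women but leaves part of the problem, because some pass 12 weeks before their first visit. With *d* = 5, full coverage and a one-quarter sweep, the share identified in time among those under way is (12² − 5²)/(2 × 12 × 13) = 119/312 = 38%, against 54% later.

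The change is to wording and analysis only, since last menstrual period is already asked at each surveillance visit. It has three costs:
- The first one or two intervals of each cluster contribute few pregnancies.
- No pre-start comparison remains for this indicator.
- If the first sweep takes 6 months, a rise of about 4 to 12 points stays in the first interval, which should be shown separately or read with that in mind.

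When the result is interpreted, it may help to note that quarterly visits alone would reach roughly 46 to 62% by 12 weeks under the assumptions above. Women reporting between visits would raise this.
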